#### Secondary outcome measures

A range of secondary outcomes will be examined, including clinicians’:i.pain screening/assessment adherence scores;ii.comprehensive pain assessment quality documentation scores; andiii.Self-Perceived Pain Assessment Capabilities (Self-PAC) survey [40].

An economic evaluation will also be undertaken and will include the following outcomes: efficacy measured using the NRS pain scores, adherence scores and Self-PAC scores; resource use, including the intervention, i.e. clinician and administration time and Qstream platform; and standard CPD, including clinician time.

### Participant timeline

See Fig. 3 for the participant timeline.

### Sample size

Informed by our pilot work [30, 31] and based on a standard RCT design [41], it is estimated that a sample size of 35 participants in each arm is required. This assumes a 5% significance level and 90% power of the study with an effect size of a reduction of mean patient-reported pain rating of 1.5 (+ 2.0). Allowing for an attrition rate of 25%, and 5% for possible inclusion of covariates in the analyses, will increase the RCT sample size to 90 clinicians (45 in each arm). To achieve the trial objectives, it is estimated that 90 cancer and/or palliative care clinicians, with half (*n* = 45) in each arm is required.

### Recruitment

Each participating site/unit will be invited to nominate a ‘clinical champion’ to act as the primary point of contact with the research team. Clinical champions will provide information about the study (Additional file 1) to all eligible participants within their department and encourage attendance at study information sessions conducted by the research team.

### Consent

All potential participants will be sent an email by the site clinical champion inviting them to attend an information session about the study, conducted by the research team. This email will include the Participant Information and Consent Form (Additional file 2) and information about the Qstream™ mobile application (Additional file 3). At the information session, participants will have the opportunity to discuss the study with a research team member(s) before consenting. Consent will be undertaken by a member of the research team. Upon consenting, participants will be asked to provide their work email address so a link to the baseline survey and Qstream™ enrolment instructions can be sent to them. Potential participants who are unable to attend the information session can contact the research team directly before consenting. The consent process for all participants at all sites will be the same.

### Blinding

Study investigators are blinded to participant allocation; however, project officers collecting and managing the data will not be blinded, as the frequency of documented pain assessment between the intervention and control groups is a secondary outcome measure in this RCT.

### Methods: data collection, management and analysis

#### Data collection methods

Data will be collected at three time points during the trial—Time 1 (T1), Time 2 (T2) and Time 3 (T3) (Table 1)—as described below.

**Table 1 Tab1:** Study activities at each time point

	Study time			
	Baseline (T1)	Intervention	T2	T3
	*Immediately before intervention commencing*		*Immediately following the completion of the intervention*	*12 weeks after completion of the intervention*
Study activities				
Chart audit data collection	X		X	X
Online Participant Survey (Self-PAC Survey)	X		X	
Economic data collection	X		X	X
Wait-listed control group access online module				X

##### Chart audit data

Patient-reported pain NRS scores and clinicians’ adherence to pain screening and assessment guidelines will be extracted from patients’ inpatient/ambulatory care medical records (electronic and/or paper-based). The chart audit tool developed, tested and refined during the pilot studies will be adopted to ensure standardised data collection. Medical records of all patients in the participating units, over 30 consecutive calendar days, will be screened for audit at each study time period (T1–T3). This will facilitate capturing chart audit data within the same duration across all participating units at each study time point. Documented patient-reported pain NRS scores and guideline adherence data will be collected by trained project officers.

Eligible medical records (chart audit) will include all patients who during the three audit periods: (1) have a primary diagnosis of cancer; 2) present for cancer treatment at a participating centre and/or are referred to a specialist cancer/palliative care service; and (3) have pain at the time of first visit/appointment/admission or develop pain during the audit period. In addition to capturing patients’ basic demographics such as age, gender, length of hospital stay, medical diagnosis, and cancer and pain treatment(s), the chart audit will also capture: patients’ pain scores on admission to the service; their pain scores at discharge and/or audit date, depending on which occurs first; clinicians’ documentation pain screening/assessment actions; and whether the clinician who documented the pain screening/assessment actions was an intervention participant or non-participant (T2 and T3 only).

Chart audit data collected at baseline (T1) will be integrated into the online learning intervention and tailored to each service (see ‘Intervention’ above). At T2 and T3, project officers will also record if pain screening/assessment actions documented in the patient chart were undertaken by an intervention participant or non-participant. This will be determined by matching clinician signatures in the patient chart with participant signatures on the study consent form and cross-referencing participants with the work roster for the audit period. To facilitate identification of participants versus non-participants, project officers undertaking the chart audits will not be blinded to the group allocation. Documentation of participant versus non-participant on the chart audit tool will be by way of a de-identified code only. No identifying participant details will be recorded on the chart audit tool.

##### Participant survey

The Self-PAC survey has undergone preliminary validation [40] and will be administered at two study time points (T1 and T2) in an online format. This instrument has three distinct sub-scales with Cronbach’s alpha reporting high internal consistency reliability: seven-item pain assessment knowledge (0.944); three-item pain assessment tool knowledge (0.846); and seven-item pain assessment confidence (0.919) scales [36]. To promote participant retention, project officers will send a unique survey link to all participants and send reminder emails to participants who do not complete the survey within the required time frame, at both survey time points.

##### Economic data

Efficacy (pain NRS score; adherence and Self-PAC scores) and resource use (intervention, i.e. clinician and administration time, Qstream™ platform; standard CPD, including clinician time) data will be collected. CPD activity data will be collected via survey and a pro-rata average cost per clinician calculated using the annual CPD site allocation.

#### Data management

All hard copies from the study will be kept at the Centre for Improving Palliative, Aged and Chronic Care through Clinical Research and Translation (IMPACCT), Faculty of Health, University of Technology Sydney, [name]. The electronic list of study codes with participant details will be stored in the secure IMPACCT research drive and will be password-protected. Hard copies of data will be secured behind at least one locked door, within a locked filing cabinet. Electronic records will be protected by a password and the password will be changed at regular intervals. Data will be stored for seven years. A dedicated password protected REDCap account has been established to deliver participant surveys for this study. This account features enhanced security (SSL) and can only be accessed by authorised members of the Research Team. Survey data downloaded from the account will be password-protected and stored on a computer hard drive at IMPACCT in de-identified format. Once data has been downloaded and de-identified, the corresponding survey data will be deleted from the REDCap account.

#### Confidentiality

The participant will be enrolled into the study after the informed consent process has been completed. All consenting participants will be given a unique Participant Identification Code (ID). This will ensure that all identifying data (e.g. email address) can be removed before data analysis commences. This project ID will enable the research team to manage the data in a confidential manner. Participants are free to withdraw from the study once it has started and can do so at any time without having to give a reason. Withdrawal of consent will not affect participants’ employment at their current work site. Previously collected data may still be used in the analyses and participants will be advised it may not be possible to withdraw their data from the study results. Where possible, the reason for study withdrawal/non-completion will be collected.

#### Statistical methods

##### Statistical analysis plan

An intention-to-treat analysis will be applied to all primary and secondary outcomes. Missing data will be imputed using Multiple Imputation by Chained Equations. Should an imbalance in clinicians’ characteristics be found between groups at baseline, these characteristics will be included in the final analyses as covariates. A significance level of 5% will be adopted for refuting all test hypotheses. The intervention and wait-listed control arms will be compared on the primary and secondary outcome measures.

The primary endpoint (reduction in mean pain NRS scores) will be analysed using the Linear Mixed Method with a repeated measures approach and possible adjustments to patients’ and staff characteristics to compare the mean change in patient pain NRS scores from admission to discharge or audit date between the intervention and control groups across different time points.

The secondary endpoints will be analysed as follows:i.The frequency of comprehensive pain assessment between the intervention and control will be determined by differences between groups. As the outcome variable is a count variable without a fixed bound, Poisson regression with possible adjustments for covariates will be applied to the data.ii.A quality score will be calculated for each audited record across time and entered into the patient’s medical records. This score will reflect the quality of the pain documentation in the medical notes and will be calculated using seven items of documentation (pain severity score, location, radiation, aggravating and alleviating factors, quality and timing). One mark will be assigned to an item identified in the medical records and a summative quality score will then be calculated to represent the total amount of information recorded. A higher quality score represents a larger amount of pain assessment information recorded and a greater adherence to recommended pain assessment practices. The quality of pain assessment documentation will be determined by comparing the quality scores across time and between groups using a General Linear Model with repeated measures.iii.The mean scores of the three domains of the Self-PAC survey (pain assessment knowledge, pain assessment tool knowledge and pain assessment confidence) will be compared across time and between the intervention and control groups using the General Linear Model with repeated measures approach and with possible adjustments for covariates effects.iv.The primary objective of the cost-effectiveness analysis is to evaluate the incremental resource use, cost and consequences of adding the mHealth enabled pain assessment performance feedback intervention to standard clinician CPD activities to improve cancer pain control. A Markov decision model will be developed to estimate the cost-effectiveness of the mHealth intervention from a healthcare perspective. Healthcare resource utilisation and cost data will be estimated from a systematic literature review of the direct and indirect costs of pain in cancer patients including hospitalisations, emergency department visits, outpatient clinic appointments, medications, GP visits and investigations. Responder rates will be estimated from the project. The modelled economic evaluation will provide estimates of the incremental cost-effectiveness ratio (incremental cost per additional responder, response = a 2-point mean reduction in NRS pain score or 30% reduction in pain intensity) and the incremental net monetary benefit (INMB; monetary value of additional effects of care minus the additional costs of care) [42] at potential threshold values for responder rates and cost-effectiveness acceptability curves. Model sensitivity to variations in individual inputs and overall decision uncertainty will be assessed through probabilistic sensitivity analyses.

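### Clinician covariates hinge on an observed baseline imbalance, and admission NRS is not fixed as a covariate in the change-score primary analysis

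*Protocol article*

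**What the plan says.** The protocol article, under Statistical analysis plan, sets one firm covariate rule. Should an imbalance in clinician characteristics "be found between groups at baseline, these characteristics will be included in the final analyses as covariates". It does not say how imbalance will be judged or which characteristics will be examined.

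The next paragraph describes the primary analysis as a repeated-measures linear mixed model "to compare the mean change in patient pain NRS scores from admission to discharge or audit date between the intervention and control groups". That sentence also lets the model be adjusted for features of patients and staff, but only as a possibility, and it names none.

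Under Chart audit data, the audit is to capture each patient's "pain scores on admission to the service", the score at discharge or audit date, and several demographic and treatment items. Admission NRS is therefore available and supplies the starting value of the change score. It is not named as a covariate.

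Under Trial design, the clinician is the unit of randomisation. Under Primary outcome measure, the outcome is measured on patients.

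The three Self-PAC domains, collected at T1 and T2 (Table 1), are to be compared "using the General Linear Model with repeated measures approach and with possible adjustments for covariates effects".

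The Sample size section already budgets for covariates: "Allowing for an attrition rate of 25%, and 5% for possible inclusion of covariates in the analyses".

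**The concern.** There are two linked weaknesses.

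**The trigger.** Clinicians are randomised, so any baseline difference between the arms in their characteristics is due to chance. Such a difference says nothing about whether the characteristic affects patients' pain. A rule keyed to imbalance can bring in variables that do not matter and leave out strong predictors that happen to balance. With no criterion, the choice of model also waits until someone has looked at the baseline table.

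**The change score.** Randomising clinicians does not directly balance the patients whose charts are audited, so mean admission NRS may differ between arms. When the correlation between admission and last NRS is below 1 and the variances are similar, patients who start higher tend to fall further. An arm with more admission pain would then show a larger fall with no intervention effect. Even when admission scores balance, the change score is noisier than an analysis adjusted for admission NRS. What is at stake is precision in every case and, if admission pain differs, some bias in the primary contrast.

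**Working it through.** **Inputs from the article (Sample size).** "This assumes a 5% significance level and 90% power of the study"; "effect size of a reduction of mean patient-reported pain rating of 1.5 (+ 2.0"), where I read 2.0 as the SD of the change score; "it is estimated that a sample size of 35 participants in each arm is required".

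**Inputs assumed.** Equal variances σ² at admission and last score; correlation ρ of 0.3, 0.5 or 0.7; an admission difference D of 0, 0.5 or 1 point; one independent patient per clinician. The article gives none of these.

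**Step 1. The plan's own figure.** n = 2(z₁ + z₂)²·SD²/difference².
- Two-sided: 2 × (1.960 + 1.282)² × 4/2.25 = 37.4, so 38 per arm (39 with the t distribution).
- One-sided: 31 per arm.
- Power at 35 per arm, two-sided normal approximation: 0.88.

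The stated 35 is not reproduced. That is a separate matter and does not affect this point; 35 serves below only as a reference size.

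**Step 2. Precision.** Var(change) = 2σ²(1 − ρ). Variance after adjustment for admission NRS = σ²(1 − ρ²). The ratio is (1 + ρ)/2, and the effective SD is 2.0 × √((1 + ρ)/2).

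**Step 3. Carry-over of an admission difference.** The slope of change on admission NRS is −(1 − ρ), so a difference D shifts the change contrast by (1 − ρ)D in size.

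| ρ | Variance ratio | Effective SD | n per arm for 90% power (from 38) | Power at 35 per arm (from 0.88) | Shift, D = 0.5 | Shift, D = 1 | D = 1 shift as share of 1.5 |
|---|---|---|---|---|---|---|---|
| 0.3 | 0.65 | 1.61 | 25 | 0.97 | 0.35 | 0.7 | 47% |
| 0.5 | 0.75 | 1.73 | 29 | 0.95 | 0.25 | 0.5 | 33% |
| 0.7 | 0.85 | 1.84 | 32 | 0.93 | 0.15 | 0.3 | 20% |

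**Step 4. Simulation check.** No true effect, 35 patients per arm, 4,000 runs per setting, nominal 5% test. Entries are rejection rates.

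| ρ | Change score, D = 0 | Adjusted, D = 0 | Change score, D = 0.5 | Adjusted, D = 0.5 | Change score, D = 1 | Adjusted, D = 1 |
|---|---|---|---|---|---|---|
| 0.3 | 4.3% | 4.9% | 11.0% | 4.7% | 31.1% | 5.7% |
| 0.5 | 5.0% | 4.5% | 8.3% | 5.5% | 17.1% | 5.1% |
| 0.7 | 5.5% | 4.7% | 6.5% | 5.8% | 9.2% | 5.0% |

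With D = 0 the simulated variance ratios were 0.68, 0.74 and 0.86, close to the formula. With D = 1 they were 0.71, 0.83 and 0.89, so the precision gain shrinks somewhat when the arms differ at admission. The simulation assumes that last NRS depends on admission NRS in the same way in both arms and that nothing else differs. It confirms the algebra; it does not show that the trial's data will behave this way.

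**Step 5. Self-PAC.** With only T1 and T2, the group-by-time term of a repeated-measures model is the difference in mean change, so the Step 2 ratio applies under the same assumptions. Clinicians are randomised, so here the issue is precision alone.

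**The case against.** The strongest reply has four parts.

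**Scope.** The imbalance rule covers clinician characteristics only, and the primary-analysis sentence separately allows adjustment for patients. A reader might infer that admission NRS is excluded from the analysis. The text does not support that: it already enters as the start of the change score, and as a covariate it is optional and unnamed. This stands and limits the point.

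**Level of detail.** Naming covariates is commonly left to an analysis plan, and none is shown. That answers any complaint that a list is missing. It does not answer the trigger, which the article states as a rule and which an analysis plan consistent with it would carry forward.

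**Size.** The correlation, the admission difference and one independent patient per clinician are all assumed, and no calculation has been made of what the trigger itself does to the error rate. A reader might infer that the trigger breaks the 5% level. That is not shown: it acts on baseline data, not on outcomes. These limits stand.

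**The remedy.** Change from admission is the declared outcome. Admission scores at T2 and T3 are taken after randomisation, possibly by trained clinicians, so the intervention might affect them. Some charts may also lack an admission score. The first part has little force: in a linear model that includes admission NRS, the arm contrast is the same whether the response is change or last score. The second is a real but small downside, and the change score already uses those same scores. The third is shared, because a change score also needs the admission value.

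**Conclusion.** The point holds in a limited form. The article ties clinician covariates to an imbalance found at baseline, with no criterion and no regard to prognostic value. It leaves patient adjustment as a possibility, and it does not fix admission NRS as a covariate for a change score measured on patients who were not randomised.

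Under equal variances and ρ of 0.3 to 0.7, adjusting for admission NRS brings the variance to 0.65 to 0.85 of the change-score variance. A between-arm admission difference carries 0.7 to 0.3 of its size into the change contrast. Both ranges are illustrative. The direction follows from the design; the size cannot be obtained from the article. If the arms do not differ at admission, both analyses keep their nominal level and the loss is precision only.

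A reader might infer that the primary result will be biased, or that admission adjustment would make the arms comparable. Neither follows. No admission difference is documented, and adjustment deals with regression to the mean on one variable while other case-mix differences remain. This should be corrected, but it does not by itself invalidate the trial.

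**What to change.** - Delete the rule that makes adjustment depend on an observed imbalance.
- State in advance, to apply whatever balance is seen, that the primary mixed model includes admission NRS, site and clinician profession (doctor or nurse).
- For each Self-PAC domain, compare T2 scores between arms adjusted for T1.
- Keep the unadjusted change-score analysis as a named sensitivity analysis.
- State that adjustment reduces regression-to-the-mean bias but not all case-mix bias, and that T2 and T3 admission scores are recorded after randomisation and could be affected by the intervention.

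The cost is wording. Admission NRS and T1 Self-PAC are already to be collected, site is part of the participant ID, and profession should be known at enrolment because eligibility is limited to medical and nursing staff. The fixed terms use few degrees of freedom (5 for six sites, 1 for profession and 1 for admission NRS, so 7), and the sample size already carries a 5% allowance for covariates.

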It is recommended that a comprehensive pain assessment be undertaken for all cancer patients with an NRS pain score ≥ 2 [12, 13]. Determining the location, temporal pattern(s), exacerbating and/or relieving factors associated with the patient’s pain and ascertaining whether the pain has nociceptive or neuropathic origin(s) [14] is integral to determining a differential pain diagnosis and an individualised cancer pain management plan. Undertaking a comprehensive pain assessment is complex and too few clinicians have been formally taught how to assess across these pain domains, with most learning ‘on the run’, by observing their peers or through industry events. Yet, clinicians’ cancer pain assessment competencies [15], their understanding of the most suitable pain assessment tools, commitment and capacity to integrate pain assessment findings into clinical decision-making [16], communication skills and capacity to address their patients’ care needs within the context of multi-professional practice [17], all impact on their patients’ pain outcomes.

Unfortunately, many interventions aimed at improving clinicians’ pain assessment have had a limited effect on cancer pain outcomes [18–25]. The reasons for this failure are complex and varied and include failure to address the multiple barriers at the patient (i.e. failing to report the presence of pain), clinician (i.e. failing to adhere to recommended routine pain screening and assessment practices) [18] and organisational/system (i.e. accreditation and funding not linked to meeting pain management standards) levels. Most previous clinician-targeted cancer pain management interventions have been based on intuition, as opposed to being theoretically driven [26], which in part explains their ad-hoc success and limited transferability [16]. While a small number of previous interventions have focused on inter-professional education [18–23], not all have optimised the educational intervention ‘dose’ (strength) [18–22] or effectively managed the complexity of the intervention [20] and/or been underpinned by an evidence-based behavioural change framework [26, 27].

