#### Theoretical framework

The intervention is underpinned by the COM-B System (Fig. 2), a framework for understanding and targeting behaviour change [27]. In this framework, capability, opportunity and motivations interact to generate the desired clinical behaviour. In this study, clinicians’ capabilities include having the necessary knowledge and skills to routinely screen for pain and to proceed to complete a comprehensive pain assessment if the patient reports a NRS pain ≥ 3. Motivation energises and directs clinician behaviour including conscious decision-making about routine screening and assessing to make cancer pain screening and assessment possible. Opportunity includes all factors that lie outside of the individual that prompt clinicians to make cancer pain screening and assessment possible (access to online decision prompts and strategies for integrating pain assessment into usual care). Adopting the evidence-based spaced learning pedagogy adds strength to this theoretically driven behaviour-change intervention. The Qstream™ platform will be used to deliver the spaced learning case-based cancer pain assessment scenarios and relevant site-specific pain assessment performance data.

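### Two secondary analyses do not fit their data or outcome: a repeated-measures model for per-record quality scores, and an unbounded Poisson count for guideline adherence

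*Protocol article*

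**What the plan says.** **Quality score (secondary endpoint ii).** Under Statistical analysis plan, a seven-item score is computed for each audited record and analysed by "comparing the quality scores across time and between groups using a General Linear Model with repeated measures". Under Chart audit data, the records are those of patients in the participating units during a 30-day period at each of T1, T2 and T3. Table 1 places T3 twelve weeks after the intervention ends. The same section limits the coding of who made an entry, participant or not, to T2 and T3.

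**Adherence (secondary endpoint i).** Secondary objective i is adherence to the guideline's screening and assessment recommendations. Secondary outcome measures lists it as "pain screening/assessment adherence scores". The analysis text then reads: "The frequency of comprehensive pain assessment between the intervention and control will be determined by differences between groups". It gives the reason for the model: "As the outcome variable is a count variable without a fixed bound, Poisson regression with possible adjustments for covariates will be applied".

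**When an assessment is expected.** Background: "It is recommended that a comprehensive pain assessment be undertaken for all cancer patients with an NRS pain score" of at least 2. Theoretical framework: clinicians should "proceed to complete a comprehensive pain assessment if the patient reports a NRS pain" of at least 3.

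**The concern.** A repeated-measures General Linear Model needs the same unit measured at each time point. If the scored unit is a chart and each audit draws its own charts, nothing is repeated. The model must then either treat unrelated records as a series or rely on an aggregation that the article does not describe.

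For adherence, the guideline recommendation is conditional on a pain score, so adherence is naturally the share of eligible patients who were assessed, and a share has an upper bound. The stated premise of an unbounded count describes a different quantity, one that also reflects how long patients stay and how many of them a clinician sees.

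These two outcomes show whether clinicians' behaviour changed. They will carry much of the interpretation if the pain result is null, and adherence scores are also listed as an input to the economic evaluation.

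**Working it through.** The article states no sample size, power or error rate for these two endpoints, so there is no planned figure to reproduce.

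**1. Is there a repeated unit for the quality score?**
- *The record or patient.* The three audits are separate 30-day windows. No patient identifier carried across windows is described. Some ambulatory patients could recur, but recurrence is not the basis of sampling.
- *The clinician.* Entries are attributed at T2 and T3 only, so no clinician series starting at T1 can be formed and no T1 value can be assigned to an arm.
- *Imputation.* The plan to impute by chained equations does not fill the gap. A T1 patient who is absent at T3 was not sampled at T3. That patient does not have a missing score.

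If records are instead treated as independent although each clinician contributes *m* of them, the actual alpha is 2[1 − Φ(1.96/√(1 + (*m* − 1)·ICC))]. Both *m* and the ICC are assumed:
- *m* = 5, ICC 0.01: design effect 1.04, alpha 5.5%
- *m* = 5, ICC 0.05: design effect 1.20, alpha 7.4%
- *m* = 10, ICC 0.05: design effect 1.45, alpha 10.4%
- *m* = 10, ICC 0.10: design effect 1.90, alpha 15.5%

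**2. Does the count measure adherence?** At the same daily assessment rate *r*, a 7-day stay yields 7*r* assessments and a 14-day stay 14*r*. The count doubles while adherence is unchanged.

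**3. Error rate of a plain Poisson test.** Let φ be the variance divided by the mean (assumed). Actual two-sided alpha = 2[1 − Φ(1.96/√φ)]:
- φ = 1: 1.96/1.000 = 1.960, alpha 5.0%
- φ = 1.5: 1.96/1.225 = 1.600, alpha 11.0%
- φ = 2: 1.96/1.414 = 1.386, alpha 16.6%
- φ = 3: 1.96/1.732 = 1.132, alpha 25.8%

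A simulation (20,000 replicates, no true effect) agrees. It took 45 clinicians per arm from Sample size, and assumed 10 records per clinician and 0.3 assessments per record, so a mean of 3 per clinician. If clinicians' rates vary with coefficient of variation *c*, then φ = 1 + 3*c*²:

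| *c* | φ | formula | simulated |
|---|---|---|---|
| 0 | 1.00 | 5.0% | 5.1% |
| 0.3 | 1.27 | 8.2% | 8.0% |
| 0.5 | 1.75 | 13.8% | 13.9% |
| 0.8 | 2.92 | 25.1% | 25.4% |

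**4. What an offset does and does not repair** (same assumptions).
- If only the number of records varies between clinicians (coefficient of variation 0.5), the error is 13.5% without a log-records offset and 5.1% with it.
- If only the clinicians' rates vary (0.5), it is 13.9% without and 13.5% with. That source needs a different variance model.
- If one arm happened to document on 1.25 times as many records at the same rate per record, the count model would show a rate ratio of 1.25 and reject 49.7% of the time. With the offset the ratio is 1.00 and rejection about 5%.

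**The case against.** The best defence is that the article condenses a fuller plan. Naming Poisson regression with possible covariates does not exclude an offset, robust errors or clinician effects, and these may sit in an analysis plan that is not shown. This stands: their absence alone is no finding. What remains is the stated premise of an unbounded count set against an outcome called adherence.

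The defence can add that the Blinding section itself names frequency of documented assessment as a secondary outcome, that the quality score is also described as reflecting adherence, and that audited charts are already restricted to patients with pain. This softens the mismatch but does not remove it. The article uses adherence in more than one sense, and the listed outcome and its analysis still differ.

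A reader might infer several stronger things that the documents do not support:
- *That both tests certainly have wrong standard errors.* With homogeneous exposure and rates, Poisson holds its level (5.1% simulated). No dispersion or ICC is given.
- *That longer stays bias the comparison of arms.* Clinicians are individually randomised, so expected exposure is equal by arm. What is left is extra variance, and imbalance arising by chance or after randomisation.
- *That the three audits contain entirely different patients, or that the General Linear Model will discard most records.* The first is a likely inference that is not stated. The second is uncertain, given the planned imputation.
- *That the conflicting NRS thresholds invalidate the Poisson model.* That analysis uses neither threshold; the conflict is a separate matter.

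**Conclusion.** The point holds in two limited parts.

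The firmer part is the quality score. As described, neither the record nor the clinician supplies a T1 to T3 series by arm, so the named model does not fit the data. This rests on the audit description alone and needs no numerical assumption.

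The second part is that the analysis of outcome i targets an unbounded count where the objective and outcome list say adherence. Its effect on the error rate cannot be computed from the documents. Under assumed variance-to-mean ratios of 1, 2 and 3, the actual error of a nominal two-sided 5% test is about 5%, 16.6% and 25.8%. The article does not state sidedness; two-sided is assumed.

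Separately, the thresholds of at least 2 (Background) and at least 3 (Theoretical framework) disagree and must be reconciled before anyone can code which records were eligible for a comprehensive assessment. Which is right is not a statistical question.

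Both endpoints are secondary. The primary test and the sample size are untouched.

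**What to change.** **Quality score.** Replace the repeated-measures General Linear Model with a record-level linear mixed model, or a linear model with cluster-robust errors. Treat audit period as a between-record factor and include site effects. Cluster by the de-identified clinician code if that code distinguishes individuals, and otherwise by unit. With only six centres the number of units may be small, so unit-level robust errors would need a small-sample correction. Estimate the arm contrast from T2 and T3 records, and let T1 enter only as a unit- or site-level baseline.

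**Adherence.** Choose one of two routes:
- Analyse the proportion of eligible audited records with a comprehensive assessment, by a binomial model that allows for clustering.
- Keep the count, add a log offset for length of stay or observation time, and use a negative binomial model or cluster-robust errors. Length of hospital stay is already captured; ambulatory records would need another measure of observation time.

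**Thresholds.** Reconcile the two NRS thresholds before eligibility is coded.

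**Cost.** Wider confidence intervals and a little more analysis work. Two limits apply. The article names pain scores only at admission and at discharge or audit date, so a proportion based on every qualifying score may need data not described; the record-level proportion avoids this. Rosters are described as a means of identifying participants, so shift counts should not be assumed to be available as an exposure measure.
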